### Intervention

We will study the response to multiple exposures of different pre-selected hypoxia protocols per participant, as at present there is no conclusive evidence for the effect of different hypoxia stimuli. This will optimize the chances for any changes in outcomes being identified, and allowing the possibility of defining the optimal dose of hypoxia as a therapeutic intervention individually. The selection of interventions was based on multiple studies that investigated and reviewed the hypoxia regimes that are currently perceived as being most effective [38–43]. In this N-of-1 trial design, every participant will receive two sets of five different conditions, with one being the placebo and the other four variants of an active intervention, consisting of either intermittent or continuous hypoxia at FiO2 0.127 (~ 4000 m) and 0.163 (~ 2000 m). All interventions are administered twice to enhance intra-individual discriminative power towards a sufficiently low or high probability (see *Statistical Analysis*). As it is shown that hypoxic preconditioning effects may linger for up to four days [44], a wash-out of at least five days between sessions will be built-in. Once a week, one of the following five conditions will be administered following the order resulting from a Latin square randomization (see *Statistical Analysis*):

Active interventions:Continuous hypoxia for 45 min, at ~ 2000 m (16.3% O_2_)Continuous hypoxia for 45 min, at ~ 4000 m (12.7% O_2_)Intermittent hypoxia with 5 × 5-min at ~ 2000 m (16.3% O_2_), interspersed with 5-min normoxic recoveryIntermittent hypoxia with 5 × 5-min at ~ 4000 m (12.7% O_2_), interspersed with 5-min normoxic recoveryPlacebo intervention:Continuous normoxia for 45 min (20.9% O_2_)

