The intervention will be performed at Radboud university medical center in Nijmegen, the Netherlands. A commercially available hypoxicator will be used to deliver the hypoxic bout (*B-cat High Altitude*, the Netherlands). The hypoxicator (as an oxygen concentrator) is ISO 13485:2016 certified and uses a process called *pressure swing adsorption* to filter ambient air and to extract oxygen from that air. The principle is widely used in oxygen concentrators, but is inversely applied in the case of hypoxicators. Instead of oxygen-rich air, the resultant hypoxic gas is administered to the patient [45]. The hypoxicator is connected via medical-grade tubes to two large (> 50L) reservoir air bags that buffer the hypoxic gas mixture, which optimizes stability of the delivered FiO2. Intermittent hypoxia and the placebo situation is administered by switching a three-way Hans Rudolph® valve to either room air or the hypoxic circuitry. The intraday and between-day reliability of the hypoxicator were tested on multiple days before application in participants. Intraday variability was low (average range 0.2 percent points around desired FiO2) and between-day variability was within 0.1 percent points of desired FiO2. Seven days before the start of the first intervention, a one week at-home registration of self-reported outcomes of symptom severity will be conducted by a short daily morning survey. This assures a solid baseline of symptom severity that will be used in the Bayesian analysis (see *Statistical Analysis*).

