#### Assessor-rated outcomes

Assessor-rated outcomes are summarized in Table 3. These consist of gold-standard general motor tests (Movement Disorders Society Universal Parkinson’s Disease Rating Scale part III, or MDS-UPDRS part III) and non-motor tests (symptoms from the MDS Non-motor symptoms scale, or NMSS), supplemented with specific tests for bradykinesia (Purdue pegboard test [52]), gait (Timed Up & Go Test [53]), balance (Mini-BESTest [54]) and quantified versions of the UPDRS items on tremor and pronation-supination (performed using accelerometry). These secondary outcomes are measured 30 min post-intervention, after which hypoxic preconditioning is believed to have its initial first window effects peak. After 30 min, the acute effects of hypoxia therapy peak, as shown in people with a cervical spinal cord injury [55], with the second window only occurring approximately 3 h post-intervention.

Various selected outcomes, including the UPDRS part III, are sensitive to the Hawthorne effect: individuals with PD try to perform as good as possible due to the awareness of being observed. To mitigate such effects, the placebo condition is added, for which the multiple N-of-1 design is also particularly suited [31, 36, 56].

Baseline characteristics that will be collected include age, gender, H&Y, quality of life (Parkinson’s disease questionnaire 39 [57]) and other medication. Potential effect modifiers include levodopa-equivalent dose (LED), sleep quality (4-point ordinal scale) and physical activity (International Physical Activity Questionnaire – Short Form, IPAQ-SF [58]) and these will be measured during every pre-intervention phase.

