### Secondary study parameters

#### Bayesian analysis

We will use a Bayesian model for the analysis of individual and aggregated N-of-1 trial results. This model allows for a direct estimation of the posterior probability that a treatment results in a clinically beneficial effect [32, 71–73]. The treatment effects resulting from the four different hypoxia protocols will be estimated per level of interest (i.e. the individual and group level). Every secondary outcome scored using the 10-point Likert scale will be modeled assuming a normal distribution centered around the patient’s true mean and variance for each protocol. If the posterior probability of reaching a 0.75-point difference between the secondary outcome after treatment and at baseline is greater than 80%, treatments are considered effective. Treatments are considered ineffective if the same posterior probability is less than 20%. Every treatment day has its own baseline (pre-intervention tests are performed) in order to further reduce period effects. The minimal clinically important difference for the secondary outcome MDS-UPDRS part III and Mini-BESTest is 4. One additional analysis will be performed including baseline characteristics and effect modifiers (see *Assessor-rated outcomes)* as covariates. Bayesian analyses will be performed using *JAGS* version 3.4.1 [74], run from *R* [75] using the package *rjags* [76].

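### The Bayesian efficacy rule judges each hypoxia protocol by change from baseline, and the placebo sessions do not enter it

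*Protocol article*

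**What the plan says.** The Bayesian analysis section of the protocol article fixes the margin, both cut-offs and the comparator for the 10-point self-ratings. The criterion for success is: "posterior probability of reaching a 0.75-point difference between the secondary outcome after treatment and at baseline is greater than 80%, treatments are considered effective". The counterpart for failure is worded: "Treatments are considered ineffective if the same posterior probability is less than 20" per cent. The effects to be estimated are described thus: "The treatment effects resulting from the four different hypoxia protocols will be estimated per level of interest". The section adds: "Every treatment day has its own baseline (pre-intervention tests are performed) in order to further reduce period effects".

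The Intervention section states that "every participant will receive two sets of five different conditions, with one being the placebo". It also says of the seven-day home registration: "This assures a solid baseline of symptom severity that will be used in the Bayesian analysis".

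Under Assessor-rated outcomes, the article acknowledges that people may perform better because they are observed, and answers: "To mitigate such effects, the placebo condition is added".

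The abstract calls the trial placebo-controlled and says that efficacy rests mainly on the Bayesian analysis. The Sample size section will use group-level effects and SDs of protocols found clinically meaningful to plan the follow-up study.

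**The concern.** The rule is a before-after comparison within each active protocol. A same-day baseline reduces differences between weeks. It does not remove what happens within a session whatever gas is breathed, such as placebo response, the effect of being observed, or change during a morning spent OFF medication. Only the normoxia sessions can separate these from an effect of hypoxia, and the rule does not use them.

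The error can run both ways. Shared improvement can make an inert protocol look effective, and shared worsening can hide a real advantage. A group-level effect measured from baseline would also carry the shared change into the sample size of the follow-up study.

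**Working it through.** The plan states no error rate for the rule, so there is no figure to reproduce. The check asks how often the rule mislabels a protocol.

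**From the article:** margin 0.75 points; cut-offs 80% and 20%; 20 participants; two sessions per condition.

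**Assumed, not in the article:** SD *s* of one session's change 1.0 to 2.0 points; between-participant SD 0.5 (of the change, or of the active-minus-placebo difference); flat prior with known SDs; positive values mean improvement; the shared shift is the same in all five conditions.

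**Rule in closed form.** Effective if estimate > 0.75 + 0.8416 × SE. Ineffective if estimate < 0.75 − 0.8416 × SE.

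**Group-level SE.**
- From baseline: √[(0.5² + s²/2)/20]
- Against placebo: √[(0.5² + s²)/20]

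For a protocol exactly as good as placebo, the probability of being called effective is:

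| s | SE, baseline | SE, placebo contrast | Baseline rule, shift 0.5 | shift 0.75 | shift 1.0 | Placebo contrast, any shift |
|---|---|---|---|---|---|---|
| 1.0 | 0.194 | 0.250 | 1.6% | 20% | 67.3% | 0.01% |
| 1.5 | 0.262 | 0.354 | 3.6% | 20% | 54.5% | 0.15% |
| 2.0 | 0.335 | 0.461 | 5.6% | 20% | 46.2% | 0.68% |

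Example, s = 1.0 and shift 1.0: 1 − Φ[(0.75 − 1.0)/0.194 + 0.8416] = 1 − Φ(−0.449) = 0.673. With no shared shift the baseline rule's rate is 0.1% or less.

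**Reverse direction, group level.** Take a true advantage over placebo of 1.0 and a shared worsening of 0.5, so the mean change from baseline is 0.5. The baseline rule calls the protocol ineffective in 67.3%, 54.5% and 46.2% for s = 1.0, 1.5 and 2.0. The placebo contrast does so in 3.3%, 6.1% and 8.3%.

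**One individual, two sessions per condition.** The SE from baseline is s/√2; against placebo it is s × √(1/2 + 1/2) = s. For a protocol no better than placebo in that person:

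| s | SE, baseline | SE, placebo contrast | Baseline rule, shift 0.5 | shift 0.75 | shift 1.0 | Placebo contrast, any shift |
|---|---|---|---|---|---|---|
| 1.0 | 0.71 | 1.0 | 11.6% | 20% | 31.3% | 5.6% |
| 1.5 | 1.06 | 1.5 | 14.1% | 20% | 27.2% | 9.0% |
| 2.0 | 1.41 | 2.0 | 15.4% | 20% | 25.3% | 11.2% |

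The contrast also leaves more individuals without a verdict. With no true effect and no shared shift, the indeterminate share under the baseline rule is 1 − 0.029 − 0.587 = 38% (s = 1.0) to 1 − 0.085 − 0.378 = 54% (s = 2.0). Under the contrast it is 1 − 0.056 − 0.463 = 48% to 1 − 0.112 − 0.320 = 57%.

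**The case against.** The article is condensed, and the full model may treat placebo as the reference condition; four estimated effects for five conditions would fit that. The paired t tests in the Frequentist analysis section name no comparator and may be against placebo. So a reader might infer that placebo is used nowhere in the analysis, and the article does not support that. What remains is that the decision sentence itself is complete and names baseline. The t tests are exploratory, group-level and do not set the label.

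A reader might also infer that placebo response or OFF-state drift will determine the labels. That depends on its size, which the article does not give. With a shared shift of 0.5 points or less, false effective calls at group level are uncommon.

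Three further readings go beyond the text:
- The Study population section enriches for people whose symptoms improved at altitude and seeks at least five without that experience. That they expect benefit from the sessions is an inference.
- The home registration and the same-day baseline are not necessarily in conflict. The registration may enter the model without being the comparator in the rule. Its role needs stating.
- The 30-minute rationale is given for assessor-rated outcomes, and the same section describes a second window at about 3 hours. It does not settle which self-rating should carry the label.

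Finally, individual inference is a main purpose of the design, and there the placebo contrast is costly. That objection stands and belongs in the price of the fix.

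**Conclusion.** The point holds for the Bayesian decision rule. As written, the main efficacy label does not use the randomised control, contrary to the role the article gives placebo. The consequence is small if within-session change under normoxia is small. It becomes serious once that change approaches or exceeds the 0.75-point margin, and more so for the group than for an individual. These sizes rest on the assumed SDs, shift and flat prior; they illustrate and do not predict.

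The trial's primary outcomes are safety and feasibility, analysed descriptively, and efficacy is secondary and exploratory. The change is therefore advisable and does not undermine the trial's primary conclusions. The planned use of group effects for the follow-up study is the main reason to make it.

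**What to change.** In the Bayesian analysis section, define the treatment effect as active minus placebo in the post-session score, adjusted for the same-day pre-session score. Apply the existing 0.75-point margin and 80%/20% cut-offs to that contrast, at individual and group level. Change from baseline can still be reported descriptively for all five conditions.

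Two clarifications should go with it. The Intervention and Bayesian analysis sections should state what role the seven-day registration has. The plan should also prespecify which of the ten post-session self-ratings (seven on the day, three on later mornings), or which summary of them, sets the label. That choice is the sponsor's.

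The cost is a few sentences and one model contrast, with no new data. Under the assumptions above, group-level standard errors rise from 0.19–0.34 to 0.25–0.46 points. Individual ones rise from 0.71–1.41 to 1.0–2.0 points, all above the 0.75-point margin. More individual results will be indeterminate, and false effective calls for an individual remain at about 6 to 11%. The report should say so.

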#### Frequentist analysis

For comparison with the Bayesian analysis we will also perform an explorative analysis of the secondary outcomes. For those that are normally distributed, we will use dependent *t* tests to calculate mean treatment effects, significance levels, and confidence intervals on group level. *P* values are 2-sided, and *P* < 0.05 will be the threshold for significance for all tests. Analyses will be performed using *R* [75]*.*

### Monitoring and registration

#### Quality assurance and monitoring

The study will be monitored regarding the health, safety and rights of participants, protocol adherence and quality of data and data reporting during this trial at study initiation, twice during the study (on-site) and once at study completion. On-site monitoring visits (performed by Radboudumc or designee) will assess the progress of the study, study procedures, used study materials and identify any concerns that result from review of the subject Informed Consent documentation, study records, collected data and study management documents. The study monitor will also ensure the Investigator adheres to all applicable regulations.

#### Data safety monitoring board

A data safety monitoring board (DSMB) will be established, which will consist of a PD-specialized neurologist, an anesthesiologist, a pulmonologist, a biostatistician and a patient representative. A first interim analysis of the safety outcomes will be performed after the pilot phase of the first two subjects that are halfway through the treatment protocol (which means every treatment is already administered once), to provide the DSMB with the latest data on adverse events and recruitment. The second interim analysis after 7 participants have completed their protocol will give insight in primary as well as secondary outcomes.

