### Study population

Twenty individuals with a diagnosis of PD (established by a neurologist according to the international Movement Disorder Society criteria) and Hoehn & Yahr stages between 1.5 and 3 will be included. Higher Hoehn & Yahr stages will be excluded for two reasons: firstly because of the significantly greater damage to dopaminergic pathways in advanced PD, which might limit the identification of nigrostriatal-mediated effects of hypoxia-based interventions; and secondly because of the high burden of testing participants in the OFF state in this more severely affected population. We aim to enrich our study population with individuals that have experienced (subjective) positive symptomatic effects at high altitude. In addition, we aim to include at least five individuals without prior experience with the positive effects of high altitude on their symptoms. This enrichment approach ensures that participants are more likely to be responders and allows us to validate our approach to identify each individual’s optimal protocol for clinical benefit. We believe that the selection bias introduced by our approach is justifiable because of the study’s explorative nature. In addition, PD is a very heterogeneous disease, for which a one-size-fits-all treatment approach is unlikely to be successful. Therefore, we wish to investigate for which individuals this therapy could be beneficial and the proposed approach is likely to be most promising. Main exclusion criteria relate to cardiorespiratory comorbidity and unstable PD medication. All inclusion and exclusion criteria can be found in Table 1.

**Table 1 Tab1:** Inclusion and exclusion criteria

Inclusion criteria	Exclusion criteria
Clinical diagnosis of Parkinson’s disease by a movement-disorder specialized neurologist	Individuals with diseases leading to restrictive and obstructive pulmonary diseases, pulmonary diffusion deficits, apnea and cardiac output deficits, such as pulmonary fibrosis, COPD, sleep apnea or excessive alcoholic intake, and congestive heart failure respectively
Hoehn and Yahr staging 1.5 to 3	Arterial blood gas abnormalities at screening day
Age > 18 years	Individuals with shortness of breath or other airway or breathing-related inconvenience related to lack of dopaminergic medication will be excluded

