### Sample size

Because this is the first study in which the clinical effects of hypoxia therapy will be measured in PD and because of the study’s exploratory nature, a formal sample size calculation cannot be performed. A previously published power and sample size simulation study aggregated N-of-1 trials with multiple cycles of intervention and placebo per participant, and found that under certain assumptions N-of-1 trials needed only one-third of the sample size of an RCT to reach a similar power and type I error [36]. This was confirmed in a recent aggregated N-of-1 trial that investigated the effectiveness of the drug mexiletine in myotonia, in which the aggregated N-of-1 trial showed comparable treatments effects on a personalized Likert scale (i.e., the same outcome measure as we propose) with inclusion of 11 participants vs 57 participants in a traditional cross-over RCT [32]. Our proposed sample size of 20 was motivated by this work, in combination with the sample size consensus for feasibility studies of 20–30 [37].

The observed effect sizes and standard deviations of the different hypoxia protocols that are found to be clinically meaningful at the participant group level in this study (*N* = 20) will be used to simulate a power and sample size calculation for a future follow-up study that will be powered for efficacy using the data generated in this study.

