### Recruitment, screening and inclusion

Individuals with PD will be recruited via the web-based ParkinsonNEXT recruitment website (www.parkinsonnext.nl) and, if necessary, from the outpatient registry of our university medical center – all patients on this list have already consented to be contacted for research purposes. After a first telephone contact with the coordinating investigator, potential participants will receive an email with detailed information about the study, including an overview of necessary time investment and the risks of participation, as well as the informed consent form. Specifically, we will ask participants with a positive altitude experience to share this project in their own networks of hikers or mountaineers.

Individuals will have a consultation by telephone conducted by the coordinating investigator to answer questions about the research and the informed consent. If the participant is still interested, screening questionnaires will be sent before the physical screening day. The coordinating investigator will contact the participant by phone to check if potential exclusion criteria are met, to prevent any unnecessary participant visits. This process will be registered in a pre-screening list. In this way, a transparent overview of study pre-selection will be available. The informed consent will be completed before initiation of the screening day. The participant has the right to withdraw consent at any moment during the study period. Drop-outs will be replaced.

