#### Pilot phase

To ensure optimal safety, a pilot study of the first two participants selected for this study protocol will be deployed before conducting this study protocol at full pace. During the screening procedure, all individuals will be exposed to gradually decreasing FiO2’s until an FiO2 of 0.127 (~ 4000 m altitude) is reached. In these two individuals, the most intense intervention (continuous hypoxia at FiO2 0.127) will be administered for 45 min, to evaluate whether exhaustion in individuals with PD will limit the maximum safe duration as clinical experience is limited. In the remaining participants, the 4000 m intervention will be administered until ABG parameters have stabilized. When no serious adverse events occur, the protocol will be continued. During this pilot phase, the same stop criteria will be adopted as during the interventions.

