#### Intervention

After completion of the screening day, participants will visit the hospital on a weekly basis, for 10 consecutive weeks. Treatments and in-hospital assessments will be conducted in the practically-defined OFF phase and will therefore commence in the morning. The treatment session in the OFF state is preceded by a baseline clinical assessment and is immediately followed by a post-intervention clinical assessment and an assessment after 30 min (Table 3). The intervention is administered in a hospital by an experienced lab technician, who also continuously monitors participants during and after the intervention. During the intervention, the inhaled FiO2 is measured continuously using the COSMED® metabolic system (*Quark CPET* metabolic cart for cardiopulmonary testing, COSMED Srl, The Metabolic Company, Italy), which also measures peripheral oxygen saturation, blood pressure, respiratory rate and tidal volume. In addition, the subjective participant experience regarding dizziness, discomfort and stress is registered by the lab technician during the intervention. In addition, to maximize safety of the participants during the intervention, clear stopping criteria are defined. If these are met, the lab technician will halt the intervention (‘Stopping Criteria’, Supplementary Materials).

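### The second DSMB look is counted in completers while drop-outs are replaced, so participants lost to harm push the safety look later

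*Protocol article*

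**What the plan says.** The section on the data safety monitoring board describes two looks.

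- **First look.** "A first interim analysis of the safety outcomes will be performed after the pilot phase of the first two subjects", timed when those two are halfway, with each treatment given once.
- **Second look.** "The second interim analysis after 7 participants have completed their protocol will give insight in primary as well as secondary outcomes". No later look is described.

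Other sections fix how a participant comes to count toward the seven.

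- Recruitment, screening and inclusion: "Drop-outs will be replaced", with no distinction by reason.
- Study procedures, Intervention: "participants will visit the hospital on a weekly basis, for 10 consecutive weeks", preceded by a one-week baseline at home.
- Study procedures, Screening: a person who meets a stop criterion during the stepwise exposure, before the lowest oxygen level is reached, is excluded and replaced.
- Study population: "Twenty individuals with a diagnosis of PD" are planned. Sample size states that "a formal sample size calculation cannot be performed".
- Pilot phase: "When no serious adverse events occur, the protocol will be continued". Beyond these two pilot participants, the article states no pause or cap on starts before the second look.

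**The concern.** Safety is a main primary outcome, and the Discussion stresses how little experience there is with hypoxia in Parkinson's disease. The second look is the first described review of accumulated data beyond two people. A count of completers makes its date depend on people who tolerated all ten sessions. Someone who withdraws because of harm is exposed and replaced, yet brings the look no nearer. If harm causes withdrawals, the review comes later and after more people have been exposed. The first look does not work this way, because it is tied to an amount of exposure.

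At stake is how many of the remaining participants a review could still protect. Two participants give little warning: an event affecting 10% of people shows up at least once in two participants with probability 1 − 0.9² = 19%, and in seven with probability 1 − 0.9⁷ = 52%.

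**Working it through.** The article has no derived figure to reproduce. The seven of 20 (35%) is a stated count. The check concerns timing.

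**Inputs from the article:** seven completers, 20 planned, ten weekly sessions (nine weeks from session 1 to session 10) and a one-week baseline. **Assumed, because not stated:** starts per week *r* and the proportion *d* who stop early.

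**Step 1: no drop-out.** Participant *i* has session 1 in week (*i* − 1)/*r*. The seventh completes in week 6/*r* + 9. The number treated at least once by then is min(20, 7 + ⌊9*r*⌋).

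| *r* per week | Week of 7th completion | Treated at least once | Sessions given, of 200 |
|---|---|---|---|
| 0.25 | 24 + 9 = 33 | 7 + 2 = 9 | 78 |
| 0.5 | 12 + 9 = 21 | 7 + 4 = 11 | 90 |
| 1 | 6 + 9 = 15 | 7 + 9 = 16 | 115 |
| 2 | 3 + 9 = 12 | 20 | 151 |

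For example, at one per week the first seven have had 70 sessions and the next nine have had 9 + 8 + … + 1 = 45, which makes 115.

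More than half (11) have been treated once 9*r* ≥ 4, so *r* ≥ 0.44. All 20 have been treated once 9*r* ≥ 13, so *r* ≥ 1.44. Counted from entry into the baseline week to a week after the last session (11 weeks), all 20 have entered once *r* ≥ 13/11 = 1.18. Starting two pilot participants together and holding the rest for six weeks changes the calendar weeks but not the counts.

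**Step 2: drop-out with replacement.** The mean number of starters needed for seven completers is 7/(1 − *d*). With duration *D* from entry to completion, the mean time of the look is (7/(1 − *d*) − 1)/*r* + *D*, so the mean delay is 7*d*/((1 − *d*)*r*). With *r* = 1 and *D* = 11 weeks:

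| *d* | Mean week of look | Mean delay (weeks) | Chance that 20 or more have entered | Mean number already stopped |
|---|---|---|---|---|
| 0 | 17.0 | 0 | 0 | 0 |
| 10% | 17.8 | 0.8 | 18% | 1.2 |
| 20% | 18.7 | 1.75 | 49% | 2.6 |
| 30% | 20.0 | 3.0 | 75% | 4.3 |
| 50% | 24.0 | 7.0 | 96% | 9.3 |

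The delay column is from the formula. The other columns are from a simulation of 4,000 runs, whose mean weeks agree with the formula. Delay scales with 1/*r*: at 0.5 starts per week it doubles, to 3.5 weeks at 20% and 6 weeks at 30%.

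**Step 3: counting completed or stopped early.** At *r* = 1 and *D* = 11, the seventh starter has finished or stopped by week 6 + 11 = 17 at the latest. The look then falls no later than week 17 whatever the drop-out.

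**The case against.** The best counter-argument is that the effect is small and other safeguards exist. Every participant is stepped down under blood-gas control at screening. Sessions are continuously monitored with stop criteria, adverse events are checked during and after each session, and on-site monitoring covers participant safety. A halted session is not stated to mean withdrawal, and completion of the protocol is not defined, so someone with a halted session who attends later visits may still count. Harm delays the look only when it makes someone leave. All of this stands and limits the size. It does not reverse the direction, and none of these measures is a committee review of data accumulated across participants.

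Four stronger readings are tempting and are not supported.

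- **That the main phase has no trigger or planned review after a serious event.** The article is silent on this. Decision thresholds and serious-event review are commonly left to the full protocol or a DSMB charter, and neither is shown.
- **That the second look concerns efficacy only.** It covers primary outcomes, and these are safety and feasibility.
- **That the look will use completers' data only.** Completers set the time. The text does not say that others' data are left out.
- **That all 20 will already have started.** This needs roughly 1.2 to 1.4 starts per week or more, or substantial drop-out. At 0.25 per week only 9 have. Two starts per week would mean 20 people in treatment at once, about four sessions each weekday at one centre, and nothing in the article shows that this is feasible.

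**Conclusion.** The point holds as a fault in a stated timing rule. Counting completers while replacing drop-outs makes the second safety look later when more participants leave because of harm. The conclusion about direction needs no assumption beyond harm causing some withdrawals.

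The size depends on accrual and drop-out, which the article does not give. Between 9 and all 20 participants may have been treated by the look across 0.25 to 2 starts per week. At one start per week the added delay is modest up to 20% drop-out and large only at 30% to 50%. The change is cheap and worth making, but the fault does not undermine the trial.

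**What to change.** In the section on the data safety monitoring board:

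1. Open the second look when seven participants have completed or permanently stopped early. An equivalent exposure count (participants started or sessions delivered) would also serve and would match how the first look is timed.
2. State that the safety data for that look cover everyone exposed, including withdrawn and replaced participants, and say how people excluded after the screening exposure are handled.

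This takes one or two sentences, with the same committee and the same data. No dose, session rule, sample size or efficacy analysis changes. The cost is that the look may come slightly earlier with fewer complete secondary-outcome records: at 20% drop-out, at most 7 × 0.8 = 5.6 completers on average in place of seven. Any stopping threshold or rule for reviewing serious events is for the sponsor and the DSMB to set.
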